# 4. Study design

This is a prospective, single-center, single-arm Phase I clinical study designed to evaluate the safety profile (including dose-limiting toxicities), efficacy, and tolerability of neoadjuvant irinotecan liposome in combination with Epirubicin.

## 4.1 Overall design

Enrolled patients with anthracycline-resistant recurrent NMIBC will first undergo enhanced pelvic-abdominal MRI and cystoscopy to collect imaging and pathological data. Two senior urologists will determine whether the tumor is resectable via TURBT. If unresectable (Arm A), patients will receive neoadjuvant irinotecan liposome combined with Epirubicin per the dose-escalation protocol. Post-treatment efficacy will be assessed by contrast-enhanced pelvic-abdominal MRI. For patients with CR and PR, TURBT with intravesical therapy was performed following confirmation by two independent senior urologists. For patients with SD or PD, subsequent therapies were determined by the investigator’s discretion. If resectable (Arm B), TURBT will be performed followed by immediate intravesical Epirubicin (50 mg) instillation within 24 hours postoperatively. During the induction phase (weeks 1-4 post-TURBT), the treatment with irinotecan liposome combined with Epirubicin will be completed according to the dose - escalation regimen. During the maintenance phase (months 1-6 post-TURBT), intravesical maintenance instillation of Epirubicin will be conducted once a month for a total of 6 cycles. The safety and adverse reactions will be followed up from the induction phase, and the tumor recurrence will be assessed by pelvic and abdominal enhanced MRI and cystoscopy after combination treatment.

## 4.2 Dose Escalation Regimen

The dose-escalation scheme is designed based on a comprehensive evaluation of non-clinical in vitro pharmacodynamic data, existing clinical efficacy evidence and Safety profiles.

Arm A: Participants in this arm will complete the neoadjuvant therapy with irinotecan liposome (intravenous injection, once every two weeks for 1 month, dose increasing regimen: 37.6 mg/m2 and 56.5mg/m2) and epirubicin (intravesical instillation, once a week for 1 month, 50 mg).

Arm B: In the induction phase, the first three participants received a reduced dose of irinotecan liposomes (37.6 mg/m2, once every two weeks) in combination with standard intravesical EPI chemotherapy (50 mg, once a week) during the first cycle. If the combination was well tolerated, the irinotecan liposome dose was escalated to the full dose (56.5 mg/m2, once every two weeks) in the second cycle. The remaining three participants received the full dose of irinotecan liposomes (56.5 mg/m2, once every two weeks) along with standard EPI (50 mg, once a week) in both treatment cycles. Epirubicin was given at a fixed dose of 50 mg q1w for 4 cycles. In the maintenance phase, Epirubicin 50 mg q1m was intravesical instillation for a total of six cycles.

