## 4.3 Dose Escalation Principles

(1) Following the "3+3 principle", that is, three subjects were enrolled in each group, and the safety and tolerability of the first cycle were observed after administration. If no DLTS occurred, the trial proceeded to the next dose level according to the established dose-escalation protocol. If one DLT occurred, three more subjects were added at that dose level. When no new DLT occurred, the trial was continued at the next dose level. If ≥ 2 DLTS occurred, the dose level preceding that dose level was defined as MTD.

(2) The subjects with DLT were treated by the investigators according to the clinical diagnosis and treatment standards, and the dose could be delayed for no more than 2 weeks, the original dose could be maintained, or the dose level could be lowered to continue the next cycle. If no DLT occurred in the three patients enrolled in the first dose group during the observation period, the subsequent treatment was escalated to the second dose level.

(3) If more than one patient experienced DLT at the prespecified lowest dose, the lower dose was explored by the investigator.

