## 4.4 Treatment Period Follow-up

Arm A: routine blood test, liver and kidney function, coagulation function and adverse reactions were followed up every cycle after the first cycle of Irinotecan liposomal treatment. Pelvic and abdominal enhanced MRI and cystoscopy were performed after the second cycle of irinotecan liposomal treatment. The patients who achieved CR and PR were treated with TURBT combined with intravesical therapy after judged by two senior urologists. Patients with SD or PD received subsequent therapy at the investigator's discretion.

Arm B: Routine blood test, liver and kidney function, coagulation function and adverse reactions were followed up every cycle after the first cycle of Irinotecan liposomal treatment. Pelvic and abdominal enhanced MRI and cystoscopy were performed after combination treatment.

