### 15.5.3 Statistical Method

For the primary endpoint, the DLT Analysis Set (DAS) included all participants who were in the DLT evaluation period and either completed the DLT assessment or experienced a DLT during the evaluation period. This analysis set will be used for the analysis and summary of DLT events. DLT Rate = ( Number of participants with ≥1 DLT / Total evaluable participants in DAS)×100%. 95% CI will be computed using the Clopper-Pearson method.

For Secondary Endpoints, such as RFS, the median value and 95% CI are estimated and survival curves are obtained using the Kaplan-Meier method. The log-rank test is used to compare the survival between the two groups. DCR with 95% CI are calculated, and comparisons between treatment groups are performed using a Cochran-Mantel-Haenszel (CMH) test or chi-square test. Two independent samples will be compared for the differences between the two groups in QoL scores by the t-test or Wilcoxon rank sum test.

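### Section 4.2 assigns neither irinotecan dose to a cohort or cycle in Arm A, and section 15.5.3 pools the primary DLT rate over both dose levels and both arms

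*Protocol*

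**What the plan says.** **Arm A dosing.** Protocol section 4.2 gives Arm A one sentence. It opens "Participants in this arm will complete the neoadjuvant therapy with irinotecan liposome" and sets the schedule as "once every two weeks for 1 month, dose increasing regimen: 37.6 mg/m2 and 56.5mg/m2". Section 4.4 confirms two irinotecan cycles in this arm: "Pelvic and abdominal enhanced MRI and cystoscopy were performed after the second cycle of irinotecan liposomal treatment".

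**Arm B dosing.** The next paragraph of 4.2 works by cohort and cycle. The first three participants start at 37.6 mg/m2, and then "If the combination was well tolerated, the irinotecan liposome dose was escalated to the full dose" in cycle 2. For the others, "The remaining three participants received the full dose of irinotecan liposomes (56.5 mg/m2, once every two weeks") in both cycles.

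**Escalation rule.** Section 4.3(1) is a 3+3 rule and names no arm: "three subjects were enrolled in each group, and the safety and tolerability of the first cycle were observed after administration". Section 4.3(2) adds that, if the first dose group of three has no DLT, "the subsequent treatment was escalated to the second dose level".

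**Size.** Section 5 plans 6-9 subjects per arm, 12-18 in all.

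**Primary analysis.** Section 15.5.3 defines the DLT rate as participants with at least one DLT divided by "Total evaluable participants in DAS", with a Clopper-Pearson 95% interval. The formula has no term for dose level or arm.

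**The concern.** DLT incidence is the primary endpoint, and 4.3(1) is the only rule that decides whether a dose level is acceptable. That rule judges the first cycle. It therefore works at 56.5 mg/m2 only if some participants start there.

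For Arm B, 4.2 makes sure that three do. For Arm A it does not say. A site following the Arm A sentence could give 37.6 then 56.5 mg/m2 to each participant, or could run a 37.6 cohort followed by a 56.5 cohort. The two differ in the dose that individual patients receive and in what the arm can say about 56.5 mg/m2. Arm B is not an obvious stand-in, because it is treated after TURBT while Arm A is treated with the tumour in place.

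The pooled rate in 15.5.3 adds to this. The trial escalates dose in two differently treated arms, but its primary estimate mixes first cycles at both levels and from both arms. One summary number can then look reassuring about the higher dose on the strength of participants who started at the lower one.

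**Working it through.** **Inputs.** Two infusions per participant (every two weeks for one month, 4/2 = 2; section 4.4 agrees). Doses 37.6 and 56.5 mg/m2 (4.2). First-cycle window, three per group, three more after one DLT (4.3(1)). 6-9 per arm (section 5). One DLT proportion over the DLT Analysis Set (DAS) with a Clopper-Pearson interval (15.5.3). The protocol states no power or target DLT rate, so there is no plan figure of that kind to reproduce.

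**1. Which scheme do the sections support for Arm A?**
- For cohorts: 4.3(1) speaks of groups of three, a next dose level, and adding subjects at a level; 4.3(2) names a first dose group.
- Also for cohorts: the possible arm totals under a two-level 3+3 (level 1 + level 2) are 3+0 = 3, 6+0 = 6, 3+3 = 6, 3+6 = 9, 6+3 = 9 and 6+6 = 12. The planned 6-9 matches the paths that clear level 1 with at most one expansion.
- For within-participant escalation: two doses are listed for exactly two cycles, in a regimen that each participant is to complete. The 4.3(2) phrase "the subsequent treatment was escalated to the second dose level" fits the same patients' next cycle as well as the next cohort.
- Neutral: section 4.1 refers only to the escalation scheme without describing it. The synopsis uses the same dose phrase for both arms.

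Cohorts are the better-supported reading, but no section excludes the other.

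**2. First cycles at 56.5 mg/m2 in Arm A** (six participants, escalation proceeding without expansion):
- Cohorts: 3 of 6.
- 37.6 then 56.5 in everyone: 0 of 6.

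**3. Planned irinotecan over two cycles.**
- First three in Arm A: 2 × 37.6 = 75.2, or 37.6 + 56.5 = 94.1 mg/m2; 94.1/75.2 = 1.25.
- Later Arm A participants: 37.6 + 56.5 = 94.1, or 2 × 56.5 = 113.0 mg/m2; 113.0/94.1 = 1.20.

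Adopting cohorts settles the second line (113.0) but not the first. Nothing says whether the first Arm A cohort stays at 37.6 in cycle 2 or moves up as in Arm B.

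**4. The pooled rate.** Take six evaluable participants per arm and no DLTs. With zero events among n, the Clopper-Pearson 95% upper limit is 1 − 0.025^(1/n).

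| Denominator | n | Upper limit |
| --- | --- | --- |
| Whole DAS, both levels and arms | 12 | 1 − 0.025^(1/12) = 26.5% |
| Cycle 1 at 56.5, both arms (cohort reading) | 6 | 1 − 0.025^(1/6) = 45.9% |
| Cycle 1 at 56.5, one arm | 3 | 1 − 0.025^(1/3) = 70.8% |

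With DLTs the same dilution appears in the estimate. Two DLTs among three starters at 56.5 in one arm (2/3 = 66.7%) would stop escalation under 4.3(1), yet they enter the pooled rate as 2/12 = 16.7%.

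The make-up of the pooled denominator also depends on the Arm A reading. First cycles at 56.5 are 3 + 3 = 6 of 12 under cohorts, and 0 + 3 = 3 of 12 if Arm A escalates within participant.

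**The case against.** The best reply is that a reader who reconciles the sections would choose cohorts. Section 4.3 is written for both arms, its vocabulary is that of cohorts, and 6-9 per arm is what a two-level 3+3 needs in each arm. The synopsis applies the same dose phrase to Arm B, where 4.2 shows that it includes a group starting at 56.5 mg/m2. This stands. It rules out one tempting inference, that the protocol prescribes 37.6 then 56.5 for every Arm A participant and so defeats its own rule. The Arm A sentence attaches neither dose to a cycle, and the phrase it uses does not carry that meaning in Arm B.

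The reply does not close the gap. The cohort scheme for Arm A has to be inferred where Arm B's is written down, and the inference does not supply the first cohort's cycle-2 dose. The first-cycle rule does not need that dose, but whoever prescribes does.

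A second reply is that tables by dose and arm belong in a statistical analysis plan, and that 15.5.3 does not forbid them. That is correct as far as it goes. But 15.5.3 is not silent: it fixes the primary rate, and the denominator it fixes is the whole DAS. The point concerns that stated choice.

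A third reply is that the MTD is not a listed endpoint. This is also correct and limits the consequence. DLT incidence is the primary endpoint, however, and 4.3(1) governs escalation whatever the endpoint list says.

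**Conclusion.** The point holds as an unresolved dosing instruction in Arm A together with a primary DLT estimate that is too coarse for a dose-escalation trial. It should be corrected, and it does not show that the design fails.

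- **Arm A.** Cohorts are favoured but not written. Under the other permitted reading, Arm A first cycles at 56.5 mg/m2 fall from 3 of 6 to 0 of 6, and 4.3(1) has nothing to judge at that level within the arm. The two-cycle dose is uncertain by 25% for the first three participants, even with cohorts, and by 20% for later ones until cohorts are stated.
- **Pooling.** With six evaluable per arm and no DLTs, the stated analysis gives an upper limit of 26.5%, while the evidence at 56.5 in one arm gives 70.8%. This holds wherever an arm has three starters at 56.5, which 4.2 already sets for Arm B. The counts of six per arm and zero DLTs are illustrative.

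A reader might infer that 56.5 mg/m2 would go untested in the trial. The documents do not support that, because Arm B has three participants who start there. A reader might also want to compare the chance of detecting an excessive DLT rate under the two Arm A readings. The comparison would not be informative: without first cycles at 56.5 the chance is zero by construction, and the other side needs a true DLT rate that the protocol does not give and, for the full rule, an arm expanded to nine.

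**What to change.** - **Section 4.2.** Write Arm A as Arm B is written, with the cycle-1 and cycle-2 dose for each cohort. To agree with 4.3(1), the first three start at 37.6 mg/m2 and a second cohort starts at 56.5 mg/m2. The first cohort's cycle-2 dose should be stated outright: 56.5 if tolerated, as in Arm B, or 37.6. If the investigators do intend 37.6 then 56.5 for every Arm A participant, the protocol should say so and add that Arm A alone supports no first-cycle DLT conclusion at 56.5 mg/m2.
- **Section 15.5.3.** Report the DLT rate with its Clopper-Pearson interval by cycle-1 dose level and arm, and keep the rate over the whole DAS as a supplement.

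The cost is a few sentences of protocol text and one additional table. Intervals by level and arm will be wide, as the evidence at each level warrants. No patients are added.

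### Arm B gives participants 1-3 the 56.5 mg/m2 dose in cycle 2, but the protocol does not say how a DLT in that cycle counts or make participant 4 wait for it

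*Protocol*

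**What the plan says.** **Dosing in Arm B (section 4.2).** Participants 1-3 receive 37.6 mg/m2 in the first irinotecan cycle. The step up within a participant is conditional, "If the combination was well tolerated", and then "the irinotecan liposome dose was escalated to the full dose (56.5 mg/m2, once every two weeks) in the second cycle". For the others, "The remaining three participants received the full dose of irinotecan liposomes" in both cycles. Section 4.2 does not make their start depend on what happened in cycle 2 of the first three.

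**The decision rule (section 4.3).** Item (1) sets the 3+3 scheme: "three subjects were enrolled in each group, and the safety and tolerability of the first cycle were observed after administration". With no DLT, the next level opens. With one, "If one DLT occurred, three more subjects were added at that dose level". With two or more, "the dose level preceding that dose level was defined as MTD". Item (2) adds a condition for moving up: "If no DLT occurred in the three patients enrolled in the first dose group during the observation period". It gives that observation period no length.

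**The primary endpoint (sections 3.1 and 15.5.3).** The primary endpoint is DLT incidence and frequency. The DLT analysis set holds participants who "were in the DLT evaluation period and either completed the DLT assessment or experienced a DLT during the evaluation period". That period has no stated length either, and the DLT rate is one proportion over the whole set, with no attribution to the dose at onset.

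**Other safeguards.** Adverse reactions are followed in every cycle (section 4.4). The study may be suspended or ended for unacceptable risk (section 6.5) or paused after an SAE (section 16). None of these is linked to the MTD decision.

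**The concern.** If participants 1-3 step up, they are the first in Arm B to receive 56.5 mg/m2, and they do so in cycle 2. The only window named for the rule is cycle 1, which for these three is the 37.6 mg/m2 cycle. So the earliest evidence on the dose to be judged has no stated role in judging it.

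Two consequences follow if the text is applied as written:

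- Two DLTs at 56.5 mg/m2 in participants 1-3 would reach the rule's own threshold of two but would not set it off.
- Participants 4-6 could start at 56.5 mg/m2 while those events are still developing, because nothing makes them wait.

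DLT is the primary endpoint and determines the MTD, so the gap affects both the safety of the next patients and the trial's main conclusion. Cohort release and the MTD decision are matters of trial conduct. They belong in the protocol and are not something to leave to a statistical analysis plan.

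**Working it through.** **1. The plan's own figure.** Section 5 gives 6-9 per arm and 12-18 in total: 2 x 6 = 12 and 2 x 9 = 18, which reproduces. Three participants starting at 37.6 mg/m2 plus three or six starting at 56.5 mg/m2 make 6 or 9, so the arm size leaves room for 3 to 6 starts at the higher dose.

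**2. Timing.** Two irinotecan cycles fit into the four-week induction phase (sections 4.1 and 4.2), so a cycle is about two weeks. Once participants 1-3 clear cycle 1, section 4.3 opens the next level. Participant 4 could then start at about the time participant 3 receives a first dose of 56.5 mg/m2.

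**3. Does any section close the gap?**

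| Place | What it covers | Assigns a cycle-2 DLT to 56.5 mg/m2? | Holds participant 4? |
|---|---|---|---|
| 4.3(1) | first cycle of each group | no | not for cycle 2 |
| 4.3(2) | observation period, no length | no | not for cycle 2 |
| 4.4 | follow-up of reactions each cycle | no | no |
| 6.5, 16 | discretionary stop or pause | no | only by discretion |
| 7 | consecutive enrolment | no | no |
| 15.5.3 | DLT evaluation period, no length | no | no |

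**4. Size on the literal reading.** The protocol gives no DLT rate. Let p be the assumed DLT risk at first exposure to 56.5 mg/m2. Take it as independent between participants and equal for participants 1-3 (in cycle 2) and for those who start at that dose (in cycle 1). All three of participants 1-3 are escalated.

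- Two or more DLTs among participants 1-3: A = 3p²(1-p) + p³
- Level accepted on those who start there (0 of 3, or 1 of 3 followed by 0 of 3): B = (1-p)³ + 3p(1-p)² x (1-p)³
- Both: A x B
- Mean number of further starts at 56.5 mg/m2, given A: 3 + 3 x 3p(1-p)²
- The same mean, given also that the dose is accepted: 3 + 3 x [3p(1-p)⁵ / B]

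| | p = 10% | p = 20% | p = 30% |
|---|---|---|---|
| A | 0.027 + 0.001 = 0.028 | 0.096 + 0.008 = 0.104 | 0.189 + 0.027 = 0.216 |
| B | 0.729 + 0.177 = 0.906 | 0.512 + 0.197 = 0.709 | 0.343 + 0.151 = 0.494 |
| A x B | 0.025 | 0.074 | 0.107 |
| Mean further starts given A | 3.7 | 4.2 | 4.3 |
| Mean further starts given A and acceptance | 3.6 | 3.8 | 3.9 |

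**5. Effect of a stop for two or more cycle-2 DLTs, with the rest of the rule unchanged.** The chance of accepting 56.5 mg/m2 becomes (1 - A) x B:

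- p = 10%: 0.972 x 0.906 = 0.881, down from 0.906
- p = 20%: 0.896 x 0.709 = 0.635, down from 0.709
- p = 30%: 0.784 x 0.494 = 0.388, down from 0.494

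**The case against.** **The text can be read more kindly.** The sentence in 4.3(1) on two or more DLTs is not itself limited to cycle 1, and 4.3(1) and 4.3(3) both speak of DLTs by dose level. An investigator could fairly treat a DLT on 56.5 mg/m2 as belonging to that level whenever it occurs. This stands, and it limits the point. A reader might infer that the protocol excludes cycle-2 DLTs from the MTD decision; the documents do not say so. They are silent, and the harm computed above is conditional on the literal reading. The kinder reading still leaves participant 4 free to start before cycle 2 of participants 1-3 is known.

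**Counting first cycles only is ordinary in a 3+3.** It also avoids carry-over from an earlier dose. That is true of the usual scheme, in which participants do not change level within the window that matters. Here the protocol itself creates earlier exposures at the dose under decision.

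**Other safeguards exist.** Cycle-2 reactions are followed, and the study can be paused or ended. These measures are discretionary and do not lead to an MTD decision.

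**A stronger remedy is tempting.** One might pool participants 1-3 and 4-6 and cap the level at six. The present rule does not support that, because it requires three more subjects after one DLT. With 0 of 3 in participants 1-3 and 1 of 3 in participants 4-6, a cap would accept the dose without that expansion. The chance of this pattern is (1-p)³ x 3p(1-p)² = 18, 20 and 15% at p = 10, 20 and 30%. Multiplied by 1 - (1-p)³, the chance that the expansion would have stopped the level, this gives 4.8, 9.6 and 9.9% of trials accepted that the present rule would have stopped. The cap would remove a safeguard about as large as the one gained.

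**Conclusion.** The gap is real and should be fixed. The protocol provides for 56.5 mg/m2 in cycle 2 of participants 1-3, names only the first cycle as the window for its rule, and neither says how a cycle-2 DLT counts nor makes participant 4 wait for it. The silence is plain from sections 4.2, 4.3 and 15.5.3 and needs no assumed rate.

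The size of the harm is less certain. If the rule is applied literally, the 56.5 mg/m2 dose would be accepted despite two or more DLTs in the first three participants exposed to it in 2.5, 7.4 and 10.7% of trials at assumed risks of 10, 20 and 30%. Whenever two or more such DLTs occur, 3 to 6 further participants could start there. These figures assume independence, equal risk in both groups and escalation of all three. Risk in cycle 2 could be higher through cumulative exposure, or lower because these participants had already tolerated 37.6 mg/m2. The point is confined to Arm B, where section 4.2 sets out the step by participant.

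**What to change.** Amend sections 4.3 and 15.5.3 as follows:

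1. Attribute a DLT to the dose being given at its onset, and include in the DLT evaluation period the first cycle at 56.5 mg/m2 after escalation within a participant.
2. Start participant 4 at 56.5 mg/m2 only after cycle 2 of the escalated participants among 1-3 has been reviewed.
3. If two or more of them had a DLT at 56.5 mg/m2, stop that level and make 37.6 mg/m2 the MTD.
4. Otherwise apply the existing 3+3 rule, unchanged, to participants who start at 56.5 mg/m2.

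Keep the expansion by three after one DLT, with no cap at six, and keep the no-DLT condition in 4.3(2) for moving up.

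**Cost.** This is a text amendment with no new procedures, and a wait of about two weeks before participant 4. The rule becomes slightly conservative, because cycle-2 events may reflect cumulative exposure: at a true risk of 10%, acceptance falls from 0.906 to 0.881. A single cycle-2 DLT would be recorded at 56.5 mg/m2 but would not by itself change the decision on later participants.
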